## Secondary objectives

1. To investigate the safety and tolerability of celgosivir

Hypothesis: The proportion of patients experiencing adverse events (AEs) or serious adverse events (SAEs) will be the same or lower in patients taking celgosivir than those taking placebo.

1. To investigate the effect of celgosivir on the time to viral clearance of dengue fever patients

Hypothesis: The time of viral clearance will be shorter for patients taking celgosivir than for those taking placebo

1. To investigate the effect of celgosivir on the serum NS1 of dengue fever patients

Hypotheses:

1. The mean serum NS1 concentration between Day 2 and Day 5 inclusive will be lower for patients taking celgosivir than for those taking placebo after adjusting for primary and secondary infection
2. The time to NS1 clearance will be shorter for patients taking celgosivir than for those taking placebo
3. To investigate the effect of celgosivir on the change in leukocyte and platelet counts of dengue fever patients

Hypothesis: The maximal change from baseline in leukocyte and platelet counts from Day 2 to Day 5 will be lower in patients taking celgosivir than those taking placebo

1. To investigate the effect of celgosivir on hemoconcentration in dengue fever patients

Hypothesis: The mean maximal hemoconcentration from Day 2 to Day 5 will be lower in patients taking celgosivir than those taking placebo

1. To characterize the population pharmacokinetics (PK) of celgosivir

Hypothesis: The clearance and volume of distribution of celgosivir will be dependent on weight and independent of age and sex.

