Upon admission, a clinical examination will be conducted, including ECG and chest X-ray. Blood samples will be taken for baseline assessments - viremia, quantitative NS1, IgG specific for previous dengue infection, hematology and coagulation, clinical chemistry, immunological profile, pre-dose pharmacokinetics, and DNA and RNA analysis. Urine will be collected for a pregnancy test (female patients only) and urine protein/ creatinine ratio and urinalysis (all patients). The patient will be asked to complete a visual analog scale for pain (VASP). The patient will then be randomized to placebo or celgosivir group. Capsules will be administered without food from Day 1 to Day 5. Patients will be placed on a special diet of protein, vitamins, and glucose containing minimal complex sugars or starches. Oral fluid intake, urine output, and stool frequency and consistency will be recorded, as well as any adverse events. Daily clinical exams will be conducted. Blood samples will be drawn daily while in hospital for hematology and clinical chemistry, viremia, quantitative NS1 levels, and immunological profiling (RNA expression levels and cytokines). Any subject who has a platelet count drop of ≥50,000/mm3 over a 24 hour period will require full blood count monitoring every 12 hr henceforth until platelet count trend reverses. Urinalysis will be conducted daily, and a sample of urine will be reserved for PK drug levels. Patients also will be asked to complete a VASP daily. Pain medications and any other concomitant medications will be recorded (date/time of ingestion and amount). Over the course of the hospital stay, eight blood samples will be obtained for pharmacokinetic assessments: one pre-dose sample will be taken on Study Day 1, three samples will be obtained on Study Days 2 through 4 between 1 to 3 hr after ingestion of drug (peak levels), and four samples will be obtained on Study Days 2 through 5 immediately prior to ingestion of the next dose (trough levels). The date and time of pharmacokinetic blood draws will be recorded on the CRF. On Study Day 5, after blood draws, administration of the last dose, safety assessments, determination of risk for DHF or DSS, and satisfactory clinical status, the patient will be discharged. Patients at risk for or who have dengue hemorrhagic fever (DHF) or dengue shock syndrome (DSS) will be transferred to a medical ward of the hospital until fit for discharge. Patients who progress to DHF or DSS may require intravenous fluids, platelet and/or blood transfusions and evaluations from other clinical specialists. They will be treated according to standard of care for DHF and DSS--primarily bed rest, fluids, as well as fever and pain medications (supportive therapy).

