# Statistical Considerations

## Sample size calculation

To achieve 80% power to detect a difference of one log viremia reduction between the celgosivir treated group and the placebo group, assuming a standard deviation of one log, a sample size of 14 for each group (28 total) is required for a 5% one-sided type I error. With a sample size of 25 in each group (50 total), we are able to detect a difference of 0.7 log viremia reduction at a standard deviation of one log (equivalently a one log reduction at a standard deviation of 1.4 log) at 80% power.

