## Statistical analysis

A detailed statistical analysis plan will be prepared prior to unblinding.

General

Continuous variables will be summarized using mean and standard deviation. Categorical variables will be summarized by frequency and percentage. Percentages will be rounded to one decimal place and, therefore, may not always add up to 100. All statistical tests will be set at a 5% level of significance. All confidence intervals will be 95% and two-sided. Statistical analyses will be performed using SAS version 9.3.

Demographic and baseline characteristics

Descriptive statistics will be used to summarize demographics and baseline information and to assess balance between the two groups (mean, standard deviation, minimum, maximum, and median for continuous variables; frequency and percent for categorical variables).

Analysis population

Statistical analysis for efficacy data will be carried out on an intention-to-treat (ITT) basis. An ITT set is defined as all patients who signed the informed consent form for the study enrollment and obtained an enrollment number. The treatment group of patients in the ITT set is the planned treatment group, i.e., according to the randomization list planned prior to the study commencement.

Statistical analysis for safety data will be carried out on an as-treated basis. An as-treated set is defined as all subjects who signed the informed consent form for the study enrollment and obtained an enrollment number. The treatment group of patients in the as-treated set is according to the treatment actually received.

Primary outcome

The primary outcomes include the mean of virological log reduction at Day 2, Day 3 and Day 4 and fever AUC above baseline. The virological log reduction of each patient will be measured at Day 2, Day 3 and Day 4 when they are inpatients. The mean of these three measurements will be computed for each patient, and then be compared between the two groups by a two-sample, one-sided t-test. The body temperature of each patient will be measured at baseline and from Day 1 to Day 5, and a curve of the temperature will be plotted. The area under this curve but above the baseline value will be computed for each patient, and then be compared between the two groups by a two-sample, one-sided t-test.

Secondary outcomes

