Viral clearance is indicated by an “undetectable” lab test results in the Dengue PCR at baseline, Day 2, Day 3, Day 4, Day 5 and Day 7. The time from baseline to viral clearance will be analyzed using a Kaplan-Meier analysis.

Serum NS 1 is measured by lab test results of “Dengue Non-structure protein 1”. The mean serum NS 1 between day 2 and Day 5 inclusive will be computed for each patient, and compared between the two groups using linear regression, adjusting for primary vs secondary infection. NS1 clearance is indicated by an undetectable lab test result in the NS1 assay. The time to NS1 clearance will be analyzed using a Kaplan-Meier analysis and compared using log rank test.

Leukocyte is measured by lab test results of “Urinalysis”, while platelet count is measure by the lab test results of “Hematology”. Both outcomes will be measured at baseline, Day 2, Day 3, Day 4 and Day 5. The maximum changes from baseline in leukocyte and platelet counts between Day 2 and Day 5 will be computed for each patient, and compared between the two groups using a two-sample t-test.

Hemoconcentration is defined as the hemaocrit at each day compared to that at Day 15. If the reference value at Day 15 is not available, use the value at Day 10. If both values at Day 10 and Day 15 are not available, the patient will be treated as a missing case. The mean maximal hemoconcentration from Day 2 to Day 5 will be computed for each patient, and compared between the two groups using a two-sample t-test.

Clearance celgosivir and volume of distribution of celgosivir will be obtained from concentration-time date by standard PK analysis. The correlation of these PK parameters with weight, age, and sex will be examined by nonlinear mixed effects modeling.

Exploratory outcomes

The various cytokines including TNF-, IL-6, IL-12, interferon-, and MCP-1, are measured by lab test results of “Cytokines” at Study Days 1, 2, 3, 4, 5, 7, 10, and 15. The maximal change from baseline (Day 1) in these cytokines between Day 2 and 15 will be computed for each patient, and compared between the two groups using two-sample t-test.

To investigate whether patients taking celgosivir will use less analgesic medications during the study, analgesic medications recorded during the in-hospital stay and the out-patient diary will between totaled. The total will be compared between the two groups using Fisher exact test.

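### Time to viral clearance has a between-arm hypothesis but no named comparison, and the plan makes no use of baseline viremia, which would make that comparison more efficient

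*Protocol*

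**What the plan says.** The second secondary objective (Protocol section 2.2) is directional and comparative: "The time of viral clearance will be shorter for patients taking celgosivir than for those taking placebo". Section 6.2, under secondary outcomes, defines clearance as an undetectable PCR, using "lab test results in the Dengue PCR at baseline, Day 2, Day 3, Day 4, Day 5 and Day 7". The analysis is then given in full as: "The time from baseline to viral clearance will be analyzed using a Kaplan-Meier analysis".

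The next paragraph treats the parallel endpoint differently: "The time to NS1 clearance will be analyzed using a Kaplan-Meier analysis and compared using log rank test". Mean serum NS1 is to be "compared between the two groups using linear regression, adjusting for primary vs secondary infection", so covariate adjustment is already part of the plan for one secondary endpoint.

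Section 5.1 has viremia drawn on admission, before randomization and dosing: "Blood samples will be taken for baseline assessments - viremia, quantitative NS1". Table 2 confirms a baseline viremia sample. Section 5.2 describes randomly permuted blocks and names no stratification factor. On error rates, section 6.2 says "All statistical tests will be set at a 5% level of significance". It makes the two primary t-tests one-sided but does not give the sidedness of the secondary tests. It also promises a detailed SAP before unblinding.

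**The concern.** A Kaplan-Meier analysis estimates a clearance curve for each arm. It does not by itself compare the arms, yet the hypothesis is about their difference. The other between-arm secondary efficacy outcomes in section 6.2 (mean NS1, NS1 clearance, leukocytes and platelets, hemoconcentration) each come with a named comparison. Viral clearance does not.

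The natural way to fill the gap is to copy the NS1 wording and add a plain log-rank test. That overlooks a feature of this endpoint. Clearance is the time at which falling viremia crosses the detection limit, so it depends on how high viremia starts as well as how fast it falls. The primary virological endpoint is a reduction from baseline and so takes the starting level into account; time to clearance does not. With 25 patients per arm and no stratification on viremia, a plain test leaves that variation in the noise. At stake is the power of a secondary virological comparison, using a covariate that costs nothing to obtain.

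**Working it through.** **1. The plan's own power figures (section 6.1).** The protocol says "a sample size of 14 for each group (28 total) is required for a 5% one-sided type I error", for a 1 log difference with SD 1 log and 80% power. The normal formula gives n = 2(1.645 + 0.842)²(1/1)² = 12.4, so 13 per group. The t-test reaches 79.7% at 13 and 82.4% at 14, so 14 is right. At 25 per group, t-test power is 78.7% for 0.7 log with SD 1 and 80.1% for 1 log with SD 1.4. The stated figures reproduce. No power is given for time to clearance.

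**2. What an added log-rank test could detect.** With d events and equal arms, HR = exp[2(z_α + z_β)/√d]. If all 50 patients clear:
- one-sided 5%: exp[2(1.645 + 0.842)/7.071] = 2.02;
- two-sided 5%: exp[2(1.960 + 0.842)/7.071] = 2.21.

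At HR 2, power is 79% one-sided and 69% two-sided with 50 events, and 71% and 59% with 40. The unstated sidedness therefore matters by 10 to 12 points.

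**3. Why the starting level matters.** If log viremia falls linearly, crossing time = (baseline − detection limit)/decline. Assume, since the protocol gives no viremia levels, baseline mean 7 log, limit 2.5 log and placebo decline 1.0 log/day. The average placebo crossing is 4.5/1.0 = 4.5 days. One SD of baseline viremia moves it by 0.5, 1.0 or 1.6 days when that SD is 0.5, 1.0 or 1.6 log. The drug effect in step 4 gives 4.5/1.35 = 3.3 days, a shift of about 1.2 days. Baseline spread can thus be as large as the effect sought.

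**4. Calibration to section 6.1.** Days 2, 3 and 4 are 1, 2 and 3 days after baseline, so mean log reduction is 2 × decline, since (1 + 2 + 3)/3 = 2.
- A 0.7 log difference means 0.35 log/day; a 1 log difference means 0.5 log/day.
- With assay SD 0.4 (assumed), noise variance in the mean reduction is 0.16 × (1 + 1/3) = 0.213.
- The between-patient SD of decline is then √(1 − 0.213)/2 = 0.44 for SD 1, and √(1.96 − 0.213)/2 = 0.66 for SD 1.4.

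**5. Simulation.** 25 per arm, PCR at 1, 2, 3, 4 and 6 days after baseline, 1,500 replicates, one-sided 5%. Power (%) for plain log-rank / log-rank stratified at the median baseline / log-rank scores adjusted for continuous baseline log viremia:

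| Baseline SD (assumed) | 0.7 log, SD 1 | 1 log, SD 1.4 |
|---|---|---|
| 0.5 log | 78 / 77 / 79 | 77 / 75 / 77 |
| 0.8 log | 74 / 75 / 76 | 73 / 73 / 75 |
| 1.0 log | 73 / 75 / 78 | 73 / 74 / 77 |
| 1.2 log | 68 / 71 / 77 | 69 / 72 / 74 |
| 1.6 log | 60 / 66 / 73 | 66 / 70 / 73 |

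Continuous adjustment gains 0 to 1 points at SD 0.5, 4 to 5 at SD 1.0 and 7 to 13 at SD 1.6. Repeat runs gave about 0 to 3, 3 to 6 and 8 to 16 points, with false positives of about 4 to 6%. The simulation standard error of a single power figure is about √(0.7 × 0.3/1500) = 1.2 points, so differences of a point or two mean nothing. Median stratification changes power by −2 to +6 points.

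**6. Cox Wald test.** Five PCR times shared by 50 patients produce heavy ties. A Cox model with Efron ties, adjusted for baseline viremia, had a one-sided type I error of 5 to 10% in simulation. Part of its apparent gain is therefore inflated error.

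**The case against.** The strongest reply is that this is SAP detail. Section 6.2 promises a SAP before unblinding, nothing in the protocol rules out a test or a covariate, and naming the test that accompanies a Kaplan-Meier analysis is routine SAP content. That stands against one tempting inference, that the secondary hypothesis will go untested. The documents do not show that; they show only that the protocol names no comparison here while naming one for the sister endpoint.

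Second, an unadjusted log-rank test is valid in a 1:1 randomized trial, and the plan uses one for NS1 clearance. Chance imbalance in baseline viremia is already covered by the 5% error rate. This also stands: the argument for adjustment is efficiency, not validity.

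Third, the gain depends on a baseline SD that the protocol does not give. A reader might infer a large avoidable loss of power, and some inputs produce one. With a drug effect of 0.25 log/day, decline SD 0.3 and assay SD 0.4, two-sided power at a baseline SD of 1.6 log is 37% for the plain test and 61% adjusted. But those inputs imply a mean reduction difference of 2 × 0.25 = 0.50 log with SD √(0.6² + 0.213) ≈ 0.75, less spread than either planning value in section 6.1. Understating the spread in decline makes baseline viremia look more dominant than the protocol's own figures allow. Calibrated to section 6.1, the gain is smaller, and close to nil at a baseline SD of 0.5 log.

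The objection does not remove the point that a pre-dose covariate, already collected in every patient, improves this comparison at no material cost in power in these runs.

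**Conclusion.** The point holds as an incomplete specification with an inexpensive improvement. The protocol sets a directional between-arm hypothesis for viral clearance, names no comparison or sidedness for it, and makes no use of a strongly prognostic baseline value.

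Under section 6.1's effect and SD, with 25 per arm, adjusting log-rank scores for baseline log viremia is worth roughly 0 to 3 points of one-sided power at a baseline SD of 0.5 log, 3 to 6 at 1.0 log and 8 to 16 at 1.6 log, with false positives near 5%. These figures rest on assumed values for baseline level and SD, detection limit, placebo decline and assay noise, and on linear decline of log viremia. The documents support neither a claim that the hypothesis goes untested nor a claim that the power loss is large. Confidence is high on the wording gap and moderate on the size of the gain.

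**What to change.** In section 6.2, after the Kaplan-Meier sentence for viral clearance, state that:
- the arms are compared by one named test, log-rank scores adjusted for baseline log viremia as a continuous covariate;
- the test is one-sided or two-sided at 5%, whichever is chosen;
- Kaplan-Meier curves and the unadjusted log-rank test are supportive.

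Continuous adjustment is preferable to stratifying at the median: it gained more in most of the calibrated cases and needs no cut-point. Do not rely on a Cox Wald test, given the ties.

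The cost is one sentence, fixed before unblinding, with no new data or visits. The downside is a slightly more complex analysis, and little or no gain if baseline viremia varies little.

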# Objectives and hypotheses

## Primary objectives

To investigate the effectiveness of celgosivir for treating acute dengue fever in adult patients

1. Hypothesis: The mean of virological log reduction (VLR) at Day 2, Day 3 and Day 4 will be greater for patients taking celgosivir than for those taking placebo (virological endpoint)
2. Hypothesis: The AUC above baseline of the fever curve for patients taking celgosivir will be lower than for those taking placebo (clinical endpoint)

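### The regression for mean serum NS1 omits the baseline NS1 that the trial measures before dosing, and so gives up precision it could have at almost no cost

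*Protocol*

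**What the plan says.** Section 6.2 (Statistical analysis, secondary outcomes) sets the endpoint: "The mean serum NS 1 between day 2 and Day 5 inclusive will be computed for each patient". It also sets the model: the means are "compared between the two groups using linear regression, adjusting for primary vs secondary infection". Section 2.2 (Secondary objectives) matches this. The hypothesis is that "The mean serum NS1 concentration between Day 2 and Day 5 inclusive will be lower for patients taking celgosivir", with the same single adjustment for infection type.

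Section 5.1 (Methods and Assessments) provides for a pre-treatment value: "Blood samples will be taken for baseline assessments - viremia, quantitative NS1, IgG specific for previous dengue infection". Randomisation comes after that draw. Table 2 marks quantitative NS1 in the screening/baseline column and again on Days 2 to 5, 7, 10 and 15.

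The virological primary endpoint in section 2.1 is handled differently: "The mean of virological log reduction (VLR) at Day 2, Day 3 and Day 4 will be greater". It is on a log scale and relative to the patient's own starting value. In section 6.2 the leukocyte, platelet and cytokine outcomes are changes from baseline, and hemoconcentration is referred to the patient's own later hematocrit.

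**The concern.** The protocol names a method and a covariate set for NS1, so leaving baseline out is a stated choice and not a detail left open. An analysis plan that follows section 6.2 literally would compare an absolute level between arms with no reference to where each patient started. If a patient's NS1 before dosing predicts NS1 over Days 2 to 5, that predictable variation stays in the residual and widens the interval for the treatment effect.

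With 25 per arm the standard error of a chance baseline difference is sqrt(2/25) = 0.28 SD. An imbalance of 0.4 SD or more in either direction then has a probability of about 16% (normal approximation). The unadjusted estimate carries the correlation times that imbalance. Section 1 names NS1 among the viral proteins whose folding the drug is meant to disrupt, so a sharper NS1 comparison is worth having.

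**Working it through.** **Inputs from the protocol.** There are 25 patients per arm, allocated 1:1. Section 6.2 sets the level: "All statistical tests will be set at a 5% level of significance". The sidedness of the NS1 test is not stated. The hypothesis is directional and the sample size uses a one-sided 5% error, so one-sided is taken as the main case and two-sided is also shown.

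**Inputs that are assumptions.** The documents give no effect, SD, skew or baseline correlation for NS1. Assumed here: a standardised effect of 0.7 (the ratio the protocol uses for viremia, 0.7 log at SD 1), with 0.5 as a variant, and a correlation rho of 0.3 to 0.8 between baseline and the Day 2–5 mean. Because infection type is already in the model, rho is the correlation within infection type. All 50 patients are taken to contribute.

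**Step 1: reproduce the protocol's own figures (viremia).** Section 6.1 says "a sample size of 14 for each group (28 total) is required for a 5% one-sided type I error". The noncentrality is 1/sqrt(2/14) = 2.65 on 26 df, which gives power 82.4%, and 14 is the smallest n reaching 80%. With 25 per arm, power is 78.7% for 0.7 at SD 1 and 80.1% for 1 at SD 1.4. The figures reproduce, and the same method is used below.

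**Step 2: cost of omitting baseline alone.** Adjustment multiplies the residual SD by sqrt(1 − rho²), so the noncentrality is d / [sqrt(1 − rho²) × sqrt(2/25)]. There are 47 df without baseline and 46 with it. For d = 0.7 without baseline this is 0.7/0.2828 = 2.475. At rho 0.5 it is 2.475/0.866 = 2.858.

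| | No baseline | rho 0.3 | 0.5 | 0.6 | 0.7 | 0.8 |
|---|---|---|---|---|---|---|
| d 0.7, one-sided | 78.6% | 81.9% | 87.9% | 92.0% | 96.2% | 99.2% |
| d 0.7, two-sided | 67.9% | 71.9% | 79.9% | 85.7% | 92.4% | 98.1% |
| d 0.5, one-sided | 53.9% | 57.2% | 64.3% | 70.3% | 78.6% | 89.6% |
| Residual variance kept (1 − rho²) | 100% | 91% | 75% | 64% | 51% | 36% |

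In the main case the loss is 3.3 points at rho 0.3, 9.3 at 0.5, 17.6 at 0.7 and 20.6 at 0.8. The last row is also the share of the 50 patients that an adjusted analysis would need for the same precision.

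**Step 3: what scale could add.** This is a simulation of 2,000 runs per setting: lognormal NS1 with natural-log SD 1.15 (1.15/2.303 = 0.5 log10), effect 0.7 SD on the log scale, half the patients secondary with a log-scale shift of −0.5, infection type in every model, one-sided 5%.

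| rho | Raw, no baseline | Raw + baseline | Log, no baseline | Log + log baseline |
|---|---|---|---|---|
| 0.3 | 59.1% | 58.9% | 77.6% | 79.8% |
| 0.5 | 58.8% | 65.0% | 78.5% | 87.3% |
| 0.7 | 58.7% | 73.2% | 78.2% | 96.0% |
| 0.8 | 57.5% | 82.0% | 77.5% | 99.0% |

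On the log scale, adding baseline gains about 2, 9, 18 and 21 points, which agrees with step 2. From raw without baseline to log with baseline the gap is about 21 points at rho 0.3, 29 at 0.5 and 37 at 0.7. Of that, 18 to 20 points come from the scale, not from baseline. At rho 0.3 an untransformed baseline added to a skewed outcome gains nothing.

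**The case against.** The strongest reply is that the documents neither say that NS1 is analysed untransformed nor give any figure from which a loss could be computed. Section 6.2 promises a detailed analysis plan before unblinding, and transformation and handling of undetectable values are normally settled there. That stands: a raw scale is the plain reading of a mean concentration, but it is an inference. The scale part of the gap in step 3 is therefore a risk and not a property of the plan. The simulation also builds in a multiplicative effect on lognormal data, which favours the log model.

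It is also fair that NS1 is a secondary endpoint, that the sample size does not rest on it, and that a second NS1 analysis (time to clearance by log-rank test) is little affected by extreme concentrations.

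A reader might infer that a baseline imbalance makes the planned comparison biased or lets it produce false differences beyond the nominal rate. The documents do not support that. Under randomisation the unadjusted estimate is unbiased, and its standard error already allows for chance imbalance.

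None of this removes the central point. The covariate set is written down, it omits the pre-treatment value of the outcome, and that value is collected.

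**Conclusion.** The point holds as a loss of precision on a secondary endpoint. With 25 per arm, one-sided 5% and an assumed standardised effect of 0.7, omitting baseline costs about 3 to 21 points of power for rho from 0.3 to 0.8. At an effect of 0.5 the range is wider, from 3.3 points (57.2 − 53.9) to 35.7 (89.6 − 53.9). Skewed, untransformed data would add to the cost.

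It would be tempting to conclude that the NS1 comparison loses much of its power. The documents do not establish that. At rho 0.3 the cost is small. It becomes large only from about rho 0.5 to 0.6, or under strong skew, and the protocol gives neither quantity. The direction of the effect is secure, and its size is not.

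**What to change.** In section 6.2, or in the analysis plan before unblinding, add baseline quantitative NS1 to the regression beside treatment and infection type. Preferably use each patient's mean log10 NS1 over Days 2 to 5 as the outcome and log10 baseline NS1 as the covariate, and report the ratio of geometric means with its 95% interval. State whether the test is one- or two-sided.

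The cost is a few sentences and no new samples. Two consequences should be accepted openly. The log scale changes the summary from the mean concentration hypothesised in section 2.2 to a geometric mean ratio, so the wording there should follow. It also needs a pre-specified rule for values below detection, at baseline as well, because the inclusion criteria (section 3.2.1) allow entry on PCR without a positive NS1 strip. If the mean concentration is to remain the target, adding baseline on the original scale is still a reasonable minimum, though it gains less if NS1 is skewed.

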Serum or plasma samples for viremia, quantitative NS1, immunological profile, DNA and RNA analysis, and PK will be transferred to Duke-NUS, Singapore Immunology Network, National University of Singapore or other laboratories for analysis and/or storage. The period of storage will not exceed 5 years.

After all study assessments have been completed on all patients and the database is locked, unblinding will occur. The primary virological endpoint will be the mean of virological log reduction (VLR) Study Day 2 to 4 between placebo and study drug groups. The primary clinical endpoint will be a reduction in fever AUC above baseline. Secondary endpoints for antiviral activity will be time to viral clearance, serum NS1 levels, leukocyte and platelet count, and hemoconcentration.

Secondary endpoints for assessing safety and tolerability are the number and severity of all adverse events and severe adverse events related to study drug compared to placebo using the 2009 WHO classification for grading adverse drug events. In addition, eight (8) samples for celgosivir serum concentrations will be obtained for population PK analysis.

Exploratory endpoints will be concentrations of various cytokines between placebo and treated groups, and changes in RNA expression of immunomodulatory genes. The trial will also assess the validity of the VASP and concomitant usage of analgesics between placebo and treatment groups as other measures of drug activity.

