| Time (Hr) relative to first dose | -14 to 0 | | **0+/-1hr** | 0 to 3 | **11 to 12+/-1hr** | 23 to 24 | **24+/-1hr** | 24 to 27 | **35 to 36+/-1hr** | 47 to 48 | **48+/-1hr** | 48 to 51 | **59 to 60+/-1hr** | 71 to 72 | **72+/-1hr** | 72 to 75 | **83 to 84+/-1hr** | 95 to 96 | **96+/-1hr** | 96 to 99 | 144 ± 24 | 216 ± 24 | 336 ± 24 |
| **Evaluation & Administrative Assessments** |  | |  |  |  |  |  |  |  |  |  |  |  |  |  |  |  |  |  |  |  |  |  |
| Demographics | + | |  |  |  |  |  |  |  |  |  |  |  |  |  |  |  |  |  |  |  |  |  |
| Medical History | + | |  |  |  |  |  |  |  |  |  |  |  |  |  |  |  |  |  |  |  |  |  |
| Informed Consent | + | |  |  |  |  |  |  |  |  |  |  |  |  |  |  |  |  |  |  |  |  |  |
| NS1 Strip Assay - test kits provided by Duke | + | |  |  |  |  |  |  |  |  |  |  |  |  |  |  |  |  |  |  |  |  |  |
| Clinical Exam h | + | |  |  | ~~+~~ | ~~+~~ |  |  | ~~+~~ | ~~+~~ |  |  | ~~+~~ | ~~+~~ |  |  | ~~+~~ | ~~+~~ |  | ~~-~~ | ~~+~~ | ~~+~~ | ~~+~~ |
| Body Weight and Height a | + | |  |  | + | + |  |  | + | + |  |  | + | + |  |  | + | + |  |  | + | + | + |
| Vital Signs (Body Tb, BP c, PR c, O2 saturation c) | + | |  | + | + | + |  | + | + | + |  | + | + | + |  | + | + | + |  | + | + | + | + |
| Hematology (FBC and WBC differential) - EDTA tubeg | + | |  |  |  | + |  |  |  | + |  |  |  | + |  |  |  | + |  |  | + | + | + |
| PT/PTT | + | |  |  |  |  |  |  |  |  |  |  |  |  |  |  |  |  |  |  |  |  |  |
| Clinical chemistry (full renal and liver panel) - plain tube | + | |  |  |  | + |  |  |  | + |  |  |  | + |  |  |  | + |  |  | + | + | + |
| GXM (PRN)d |  | |  |  |  |  |  |  |  |  |  |  |  |  |  |  |  |  |  |  |  |  |  |
| ECG | + | |  | + |  |  |  | + |  |  |  | + |  |  |  | + |  |  |  | + | + |  | + |
| Chest X-ray | + | |  |  |  |  |  |  |  |  |  |  |  |  |  | + |  |  |  |  |  |  |  |
| Pregnancy Assay in Females (Urine) | + | |  |  |  |  |  |  |  |  |  |  |  |  |  |  |  |  |  |  |  |  |  |
| Urinalysis | + | |  |  |  | + |  |  |  | + |  |  |  | + |  |  |  | + |  |  | + |  |  |
| Urine protein/creatinine ratio | + | |  |  |  | + |  |  |  | + |  |  |  | + |  |  |  | + |  |  | + |  |  |
| Dengue IgM |  | |  |  |  |  |  |  |  |  |  |  |  |  |  |  |  |  |  |  | + |  |  |
| Dengue IgG | +  + | |  |  |  |  |  |  |  |  |  |  |  |  |  |  |  |  |  |  |  |  |  |
| Drug Administration (capsules) |  | | 4 |  | 2 |  | 2 |  | 2 |  | 2 |  | 2 |  | 2 |  | 2 |  | 2 |  |  |  |  |

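### Section 6.2 takes the leukocyte endpoint from urinalysis, although the objective and Table 2 point to the blood count

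*Protocol*

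**What the plan says.** The objective in Section 2.2 is "To investigate the effect of celgosivir on the change in leukocyte and platelet counts of dengue fever patients", and its hypothesis reads "The maximal change from baseline in leukocyte and platelet counts from Day 2 to Day 5 will be lower in patients taking celgosivir" than in those taking placebo. Section 3.1 gives the endpoint its role: "Secondary endpoints for antiviral activity will be time to viral clearance, serum NS1 levels, leukocyte and platelet count, and hemoconcentration". Table 1 also shows leukocyte and platelet count as one item, beside hemoconcentration.

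Section 6.2 then names the source of each measurement: "Leukocyte is measured by lab test results of “Urinalysis”, while platelet count is measure by the lab test results of “Hematology". On timing it says "Both outcomes will be measured at baseline, Day 2, Day 3, Day 4 and Day 5". On the derived variable it says "The maximum changes from baseline in leukocyte and platelet counts between Day 2 and Day 5 will be computed for each patient", with a two-sample t-test between the arms.

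Section 5.1 states "Blood samples will be drawn daily while in hospital for hematology and clinical chemistry". The matching row of Table 2 is labelled "Hematology (FBC and WBC differential"). Urinalysis is a separate row of that table, and Section 5.4 lists it among the data for the safety assessments.

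**The concern.** The analysis section assigns the two halves of one paired endpoint to two different specimens. Leukocytes in urine and the white cell count in blood are different quantities, and only the second belongs naturally with the platelet count and the hematocrit as a sign of drug activity. The protocol gives no reason for treating urinary leukocytes as an activity measure, and it does not say in what form a urinary leukocyte result would be reported.

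This is not a detail left open for the statistical analysis plan. The protocol names a source, and the source conflicts with its own objective. An analysis plan written faithfully from Section 6.2 would carry the error forward. One that silently used the blood count would depart from the protocol. What is at stake is whether the leukocyte hypothesis in Section 2.2 is tested at all.

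**Working it through.** The protocol states no figure on this point, so the check sets its sections side by side.

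**1. What is to be tested.** Section 2.2 has a single hypothesis for leukocyte and platelet counts: maximal change from baseline, Day 2 to Day 5. Section 2.2 does not use the word blood. That reading rests on the pairing with platelets there, on the grouping with hemoconcentration in Section 3.1 and Table 1, and on step 2.

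**2. Where the protocol measures white cells.** Table 2 puts the full blood count and white cell differential in the hematology row. No entry in Table 2 describes a leukocyte measurement in urine.

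**3. What Section 6.2 uses.** Urinalysis for leukocytes, hematology for platelets. The sentence contrasts the two panels explicitly, so it cannot be read as hematology for both.

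**4. Would the data reveal the slip?** Marks in Table 2:

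| Row | Baseline | Day 2 | Day 3 | Day 4 | Day 5 | Day 7 | Day 10 | Day 15 |
|---|---|---|---|---|---|---|---|---|
| Hematology | + | + | + | + | + | + | + | + |
| Urinalysis | + | + | + | + | + | + | | |

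Section 6.2 needs baseline and Days 2, 3, 4 and 5, which is 1 + 4 = 5 time points. Both rows supply all 5. A programmer following Section 6.2 would find a urine panel at every required time, with no gap to prompt a question.

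**5. Is anything missing for the correct analysis?** No. The hematology row covers the same 5 time points, so the blood leukocyte endpoint can be computed from data already planned.

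**6. Side question: the meaning of maximum change.** Neither Section 2.2 nor Section 6.2 says whether the change is signed, absolute or restricted to decreases. Take invented values, for illustration only: baseline 4.0, then 2.0, 1.8, 3.0 and 5.0 on Days 2 to 5.

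- Changes from baseline: 2.0 − 4.0 = −2.0; 1.8 − 4.0 = −2.2; 3.0 − 4.0 = −1.0; 5.0 − 4.0 = +1.0.
- Signed maximum: +1.0.
- Largest absolute change: 2.2, a fall.
- Largest decrease: 2.2.

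The readings can differ, and the protocol does not choose between them. This is separate from the specimen error and applies to platelets too.

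**The case against.** The strongest reply is that this is a wrong panel name in one sentence, and that the intent can be recovered. The same paragraph goes on to analyse leukocyte and platelet counts jointly, Table 2 shows where white cells are measured, and urinalysis is a safety item. Section 6.2 also promises a detailed analysis plan before unblinding, so the source can be corrected before any comparison is made. Much of this stands. It is probably a drafting slip, and it is a reason to rate the point below a critical fault. It does not remove the point, because the current text states a rule, the rule is wrong, and the urine data would fit it without complaint.

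A reader might infer more than the documents support, in three ways.

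- **That the leukocyte comparison is lost.** It is not, since blood counts are collected on exactly the days needed.
- **That a count which dips and then rebounds above baseline must be scored as a rise.** That follows automatically only if maximum change means the signed maximum, which the protocol does not say. Under the absolute reading, the example above gives a fall of 2.2.
- **That the hypothesis concerns a fall in white cells, or leukopenia.** Section 2.2 says only that the maximal change will be lower. It names no direction, and the protocol does not mention leukopenia.

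The exact algorithm for a maximum change is also something that a protocol commonly leaves to the analysis plan, so its absence here is not a fault in itself.

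**Conclusion.** The point holds as a contradiction between the analysis section and the rest of the protocol. As written, the secondary leukocyte analysis would use urinary leukocytes and would not test the hypothesis it is meant to test. It should be fixed, but it does not threaten the trial. One of the two counts in one secondary objective is affected. The two primary endpoints, the sample size and the platelet data source are untouched, and no data are at risk.

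The conclusion rests on one reading: that leukocyte count in Section 2.2 means the blood count. The pairing with platelets, the grouping with hemoconcentration and the hematology row of Table 2 all support it, and nothing in the protocol supports the alternative.

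**What to change.** In the secondary outcomes paragraph of Section 6.2, replace urinalysis with hematology (total WBC from the FBC) as the source of the leukocyte endpoint, and carry the same source into the statistical analysis plan. The cost is one sentence. No sample, visit or assay is added.

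Two optional improvements could be made at the same time, before unblinding. Neither is needed to cure the error.

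- State for both counts whether maximum change is signed, absolute or the largest decrease. The choice is for the sponsor to confirm.
- Adjust the comparison between arms for the baseline count, which is already collected.
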